**2. Background and Rationale**

**2.1 What is the problem being addressed?**

Rates of suicidal crisis among children and young people (CYP) are on the rise, with suicide rates per 100,000 adolescents having increased by 7-9% per year since 2010.^1^ Suicide is one of the leading causes of death in adolescents worldwide. In Northwest England, there has been an increase in attendances to Emergency Departments for CYP in suicidal crisis and/or for self-harm,^2^ and the number of CYP presenting is significantly worse than the UK average.^3^ Schools are a ‘universal access point’ for CYP, providing an opportunity to reach many CYP and intervene early. Suicide prevention interventions have been implemented in schools worldwide, but there are few in the UK and they have not been rigorously tested. The Multimodal Approach to Preventing Suicide in Schools (MAPSS) project, a suicide prevention intervention in Australia, has demonstrated feasibility and acceptability and is currently undergoing a randomised controlled trial (RCT) in Melbourne.^4^ The MAPPS intervention consists of three parts: suicide prevention lesson for all pupils, risk screening, and cognitive behavioural therapy (CBT) for those deemed to be at high risk for suicide ideation. However, cultural transferability of interventions cannot be assumed, and so we need to establish whether MAPSS could be effective in the UK.^5^ A recent scoping study^6^ of MAPSS conducted by the Co-PIs interviewed CYP, school staff, parents, and health professionals. All participants advocated the importance of school-based suicide prevention and gave feedback on the adaptations needed to the MAPSS intervention for the UK. The adapted MAPSS programme is being piloted across two schools to test the delivery, planning, and modifications needed. The proposed study aims to build on this work, employing a feasibility study design across six schools to assess: 1) the acceptability and safety of delivering MAPSS in a school setting in England; 2) the social validity (feasibility, utility, and acceptability) of the MAPSS intervention; and 3) the feasibility of delivering a large-scale, appropriately powered, cluster-RCT and economic evaluation of this intervention in the future.

**2.2 Why is this research important in terms of improving the health and/or wellbeing of the public and/or to patients and health and care services?**

This project aligns with the National Suicide Prevention Strategy’s critical actions and will contribute to the Zero Suicide initiative and the national awareness campaign by the ‘Three Dads Walking’.^7,8^ This year there has been increasing discussions about suicide prevention in schools following a petition by the Dads that received over 150,000, and the subsequent debate within Parliament (<https://commonslibrary.parliament.uk/research-briefings/cdp-2023-0060/>). The Baton of Hope are also developing an education charter highlighting how suicide prevention should be introduced into schools (<https://batonofhopeuk.org/>). Additionally, a national webinar hosted by The Jordan Legacy in England highlighted further the importance of including young people’s voices when designing and implementing suicide prevention curriculum content for schools (<https://thejordanlegacy.com/the-role-of-education-and-training-in-preventing-suicides/>).

Findings from the proposed study will help to inform the development and delivery of a suicide prevention intervention for CYP in schools, with the potential to improve lives and reduce the number of adolescent deaths. The cost of one suicide is approximately £1.5 million;^9^ thus, there are wider economic and societal benefits, including reduced costs associated with mental health difficulties across the life-course, and reduced strain on the NHS. In the Northwest, many CYP experience poor mental health, particularly children living in poverty. With public and patient involvement and engagement (PPIE) and stakeholder consultation, there will be enhanced interdisciplinary working, sharing of expertise and resources, and a greater sense of connectedness. Delivering the programme to 14-15 year olds provides an opportunity for early education and intervention. 50% of lifetime mental health conditions start by the age of 14 and 7.4% of 17- year-olds have previously attempted suicide,^10,11^ therefore intervening early may prevent early suicide attempts and improve adolescent mental health. This could incur long-term benefits into adulthood, as having a mental health condition and previously attempting suicide are both risk factors for future suicidal behaviours and service use.^1,12,13^

**2.3 How does the existing literature support this proposal?**

Suicide is the second leading cause of death in young people under 25 in England.^14^ Suicidal ideation and behaviour are associated with a host of negative outcomes including risk of future suicide.^15,16^ The impact of suicide on a young person’s family, friends, and wider community can be devastating, and also increases their own risk of suicide.^17^ There is therefore an urgent need to develop and test acceptable and effective approaches to preventing suicide in this population. Schools are an appropriate setting for the delivery of mental health prevention programmes, offering a ‘universal access point’ to all CYP, and have been identified as important locations for suicide prevention activities.^18^ Although school wellbeing staff may be able to provide support to pupils, CYP are often reluctant to seek help from professionals, preferring informal sources of support.^19^ School-based prevention efforts must therefore not only target school staff, but also fellow pupils.

Historically, there has been a reluctance to deliver suicide prevention efforts to pupils, due to concerns about potentially iatrogenic impacts.^20,21^ However, increasing evidence suggests that it is safe to do.^22,23^ A number of universal psychoeducation suicide prevention programmes have been tested internationally, and appear to increase knowledge, attitudes, and help-seeking intentions; some have also been associated with reductions in suicidal ideation and behaviour.^24,25^ Suicide prevention lessons such as safeTALK, a 3.5 hour lesson suitable for people age 14 and above (preventsuicide.org.uk), have been evaluated in youth populations.^18^ “Reframe IT”, an online Cognitive Behavioural Therapy (CBT) programme specifically designed for young people presenting in school with suicide risk, has also been found to be associated with reduced suicidal ideation, depression, and hopelessness in Australian CYP.^26,27^ According to international best practice, suicide prevention programmes should incorporate universal, selective, and indicated approaches.^28^ Such approaches have shown promise in both community and school settings.^29^ To date, only one study^4^ is applying rigorous economic methodology to evaluate short- and longer-term cost-effectiveness of an intervention comprising universal, selective, and indicated elements in schools.

A pilot study of MAPSS in two schools commissioned by Cheshire and Merseyside Public Health Collaborative (CHAMPS) has shown that it is feasible to recruit schools, have Papyrus deliver suicide prevention training to school staff and suicide awareness sessions to parents, for researchers to conduct surveys within the school setting at study timepoints, to identify pupils who may be at risk of suicide, deliver suicide prevention lessons with Year 10 pupils, and to recruit pupils to test the online CBT therapy programme, Reframe IT-UK. The pilot study will have been completed and written up prior to the start of this feasibility trial. Any modifications needed to the programme following on from the pilot will be discussed with the team and updated as required.

**3. Research Question**

Research question: What is the feasibility of a school-based suicide prevention programme comprising universal, selective, and indicated components in reducing suicide risk, improving risk recognition, and increasing health service use among young people aged 14-15 years in Northwest England?

MAPSS involves the delivery and evaluation of universal psychoeducation workshops (e.g., safeTALK) to school pupils, screening pupils for suicide risk (universal and selective approaches), and online CBT (Reframe IT-UK) delivered to pupils identified as being at-risk (indicated approach).

The primary aims of this study are to assess:

1. The acceptability and safety of conducting a trial of a suicide prevention programme in a school setting, operationalised in terms of adverse events and self-reported adverse consequences at post-intervention assessments.
2. The social validity (feasibility, utility, and acceptability) and implementation (including fidelity, quality, and dosage) of the MAPSS intervention, through a process evaluation consisting of bespoke quantitative surveys and qualitative interviews and focus groups.
3. The feasibility of delivering a large-scale, appropriately powered, cluster-RCT with economic evaluation in the future, including assessment of recruitment methods, retention rates, and outcome measures-and to assess links between these short-term trial outcomes and longer terms costs and outcomes.

We aim to test the following as secondary outcomes:

1. Comparison of suicide literacy and help-seeking intentions for suicidal thoughts or behaviours between the control group and pupils attending the suicide prevention workshop.
2. The identification of pupils at-risk of suicide who had not previously sought help.
3. Comparison of suicidal ideation, depression, and hopelessness between the control group and pupils in the Reframe IT-UK intervention group.
4. Rates of health-service use to inform an economic evaluation - levels of health-related quality of life.
5. Help-seeking intentions from informal sources.

**4. Research Plan/Methods**

**4.1 Design and Theoretical/Conceptual Framework**

The study will be conducted over a 2-year period (Jan 2024-Jan 2026), with 3 months for set up, 18 months feasibility, and 3 months consolidation.

This study adopts a multiphase feasibility design, consisting of 3 work packages (WP):

**WP1:** A three-month set-up stage to: i) make any adjustments to the interventions as determined from the pilot study, ii) recruit the RA, and iii) spend dedicated time recruiting schools from a diverse range of backgrounds, with two schools recruited in the first 3 months and the remaining four schools within 9 months, to enable alignment with school academic terms.

**WP2:** An 18-month feasibility study evaluating MAPSS in 6 schools: a feasibility cluster-RCT (schools as the unit of randomisation). Four schools will be randomised to receive MAPSS (intervention arm) and two schools will be randomised to continue with usual practice (control arm). Surveys will be completed by both arms at all timepoints. The trial will include i) baseline survey, ii) universal suicide prevention lesson (e.g., safeTALK) in intervention arm, iii) survey and screening 2 weeks after suicide prevention lesson, iv) an indicated Reframe IT-UK CBT intervention in intervention arm for pupils identified as high suicide risk, and usual care in control arm v) survey 2-weeks after Reframe IT-UK CBT, vi) survey 12-months post baseline.

**WP3.** A parallel process evaluation, to establish perceptions of social validity of the programme for use in the UK, and the appropriateness of the research design for effectiveness trials.

The study is facilitated by an extensive partnership with Local Authorities, schools, public advisors, professional educators, and researchers (see Letters of Support attached from collaborators and partner organisations). The specific objectives are to assess:

1. The acceptability and safety of a suicide prevention programme in schools

A mixed-methods approach will be used to determine acceptability and safety of trialling a suicide prevention programme in UK schools. The proportion of pupils who complete all agreed sessions of therapy will be recorded (>60% excellent; 40%-60% acceptable; <40% not acceptable).

Safety will be operationalised in terms of adverse events linked to the intervention (e.g., suicidal behaviour, crises, or increased self-harm), and in terms of self-reported adverse consequences at post-intervention assessments.

1. The social validity of MAPSS

Participants will complete bespoke social validity measures adapted from the Australian trial.^4^ We will also undertake a qualitative process evaluation, consisting of semi-structured interviews and focus groups in four ‘case study’ schools (see further details in section 4.7) with pupils, in addition to as many pupils as possible who dropout (estimated to be a much smaller group), to determine their experience of MAPSS, what was helpful or not helpful, and problems in completing sessions. We will also carry out interviews with teachers and members of the senior leadership team to investigate facilitators and barriers to delivering MAPSS within school. Module utilisation, attendance at suicide prevention lessons, and screening will be monitored to review whether all aspects of the programme are used and when and where they are used.

1. The feasibility of delivering a large-scale trial of this intervention in the future

Uptake and retention of participants in school-based intervention trials is a major issue that impacts the feasibility of future trials.^30^ This will be monitored through a mixed-methods evaluation encompassing quantitative and qualitative indicators. Quantitative indicators will include: a) comparisons of recruitment methods (for schools and then pupils into the study); b) successful data collection rates (low missing data); c) presence of floor/ceiling effects in collected data; d) whether responses on potential outcome measures remain static (or show ‘movement’) between baseline and follow-up; e) calculation of the precision of estimates of key parameters, which will inform a future trial. Qualitative indicators will include evaluation of the perceived mechanism of change and contextual factors impacting upon the effectiveness of the intervention for pupils and teachers. We will seek to interview participants who do not complete follow-up questionnaires to determine their reasons for not doing so and any factors that would improve completion rates. Factors that will determine stop/go procedures to a definitive trial will include: evidence that recruitment to a definitive study, using optimum recruitment pathways in one region, would be as follows: number of schools recruited at 9 months (6 excellent, 3-4 acceptable, 1-2 unacceptable), number of high-risk pupils recruited in the cluster-RCT per school (10-15 excellent, 5-10 acceptable, 0-5 unacceptable), and proportion of complete data collected (>80% acceptable). Retention will be judged by the following criteria: >80% completion excellent; 60-80% acceptable; below 60% unacceptable.

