An AE is the development of an untoward effect, undesirable clinical occurrence or medical condition, or the deterioration of a pre-existing medical condition following or during exposure to a study intervention, whether or not considered causally related to the study intervention. For the purposes of safety reporting, any research activity is considered to be part of the “study intervention”. An AE can therefore be any unfavourable and unintended clinical sign, symptom, observation, or disease temporally associated with the use of an intervention, whether or not related to the intervention. An SAE is any untoward medical occurrence that: results in death or is life-threatening (‘life-threatening’ in the definition of SAE refers to an event in which the participant was at risk of death at the time of the event, it does not refer to an event which hypothetically might have caused death if it were more severe); requires inpatient hospitalisation or prolongation of existing hospitalisation; results in persistent or significant disability/incapacity; is an important medical event that although not immediately life-threatening or result in death or hospitalisation, based upon appropriate medical and scientific judgment, may jeopardise the participant and/or require intervention to prevent one of the outcomes listed above. Outpatient treatment in an emergency department is not in itself an SAE, although the reasons for it may be (e.g., suicide attempt). Hospital admissions and/or surgical procedures planned before or during a study are not considered SAEs if the illness or disease existed (or the surgery was planned) before the participant was enrolled in the study, provided that it did not deteriorate in an unexpected way during the study.

***Assessment and documentation of AEs:*** All AEs and SAEs that arise during the trial will be recorded in the study database. The causality of AEs and SAEs (i.e., their relationship to intervention treatment) will be assessed by a suitably qualified study team member. Any SAE will be reported to the Sponsor and to the relevant ethics committees within 24 hours of the research team becoming aware of its occurrence.

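### Section 4.1 limits the adverse-event part of safety to events linked to the intervention, contradicting sections 3 and 4.14 and leaving that part without a valid control-arm counterpart

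*Protocol*

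**What the plan says.** Three places in the protocol bear on what counts as a safety event.

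- **Section 3 (Research Question), primary aim 1.** Acceptability and safety are "operationalised in terms of adverse events and self-reported adverse consequences at post-intervention assessments". Nothing is said about cause.
- **Section 4.1, objective 1.** "Safety will be operationalised in terms of adverse events linked to the intervention", with suicidal behaviour, crises and increased self-harm as examples. The sentence then adds a second component, "and in terms of self-reported adverse consequences at post-intervention assessments", which carries no attribution condition.
- **Section 4.14 (Assessment and Follow Up).** An adverse event is defined "whether or not considered causally related to the study intervention". For safety reporting, "any research activity is considered to be part of the" study intervention. "All AEs and SAEs that arise during the trial will be recorded in the study database". On causality: "The causality of AEs and SAEs (i.e., their relationship to intervention treatment) will be assessed by a suitably qualified study team member".

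Section 4.10 does not list safety under its primary outcome measures, and Table 1 in section 4.2 has no safety criterion. Section 4.1 is therefore the most specific statement of how safety will be measured.

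**The concern.** The examples in 4.1 are events that also happen without MAPSS. The trial screens for suicidal ideation, and section 4.8 expects 10% of pupils to score in the at-risk range. For such events, judging cause one pupil at a time is weak evidence. The sounder evidence is the all-cause rate in the intervention schools set against the all-cause rate in the control schools.

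A filter on linked events undoes that comparison for the adverse-event component. It takes out control-arm events that have nothing to do with the trial, which are the ones that show the background. It also makes the intervention-arm count depend on attribution decisions. The error can go either way: background events judged linked look like harm, and real excess harm judged unrelated disappears.

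This matters here because section 2.3 acknowledges historical concern about iatrogenic effects, and section 4.5 makes later delivery of the lesson in control schools conditional on its being judged safe.

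**Working it through.** The protocol states no adverse-event rate and no figure that rests on one, so there is nothing to reproduce. The check sets the texts side by side and then illustrates the size.

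**1. The definitions compared**

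| Place | Event counted | Attribution needed? |
|---|---|---|
| Section 3, aim 1 | Adverse events | No |
| Section 4.1, objective 1 | Adverse events linked to the intervention | Yes |
| Section 4.14, definition and recording | All adverse events and serious adverse events | No |

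Sections 3 and 4.14 agree with each other. Section 4.1 differs from both.

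**2. Can a control-arm event be linked?** On one reading, yes. Section 4.14 counts research activity as part of the study intervention, and section 4.1 has both arms complete the surveys at every timepoint. Distress brought on by a survey or by screening in a control school could qualify. But the causality sentence in 4.14 explains causality as relationship to intervention treatment, which control pupils do not receive. On either reading, a control pupil's self-harm that is unrelated to any trial activity does not count, so the background rate is lost.

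**3. Illustration of size**

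Inputs from section 4.6: about 54 at-risk pupils in the intervention arm and about 27 in the control arm. Assumptions, not from the protocol: the same true all-cause rate *r* in both arms (5%, 10%, 20%), a share *s* of intervention-arm events judged linked (25%, 50%, 100%), and no control events judged linked.

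Apparent difference = *r* × *s* − 0. True difference = *r* − *r* = 0.

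| *r* | All events expected (54 v 27) | Counted, *s* = 25% | Counted, *s* = 50% | Counted, *s* = 100% | Apparent difference (points) |
|---|---|---|---|---|---|
| 5% | 2.7 v 1.35 | 0.675 v 0 | 1.35 v 0 | 2.7 v 0 | 1.25 / 2.5 / 5 |
| 10% | 5.4 v 2.7 | 1.35 v 0 | 2.7 v 0 | 5.4 v 0 | 2.5 / 5 / 10 |
| 20% | 10.8 v 5.4 | 2.7 v 0 | 5.4 v 0 | 10.8 v 0 | 5 / 10 / 20 |

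The spurious difference runs from 0.05 × 0.25 = 1.25 points to 0.20 × 1 = 20 points. Because it equals *r* × *s*, it does not depend on the number of pupils; only the event counts do.

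**4. The opposite error.** Suppose the true rates are 20% in the intervention arm and 10% in the control arm, a true difference of 10 points. With 25% of intervention-arm events judged linked, the counted rate is 0.20 × 0.25 = 5%, against 0 in control. The apparent difference is 5 points, half the true one.

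**5. A zero produced by the rule.** A genuine 0 of 27 has an exact 95% upper limit of 1 − 0.025^(1/27) = 12.8%, ignoring clustering by school. A zero that the counting rule produces carries no such information, yet it would look the same in a table.

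**6. After the change.** Counting all events under the 4.14 definition gives the expected counts in the second column of the table, and the expected difference is 0 when the true rates are equal.

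**The case against.** A reader might infer that safety counts only linked events, that control pupils cannot have one by definition, and that the arms therefore cannot be compared on safety. The protocol does not support any of the three.

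- The 4.1 sentence has a second component, self-reported adverse consequences, with no attribution condition.
- Section 4.14 treats research activity as part of the study intervention, so a control event tied to a survey or to screening could qualify. A zero in the control arm is likely on the narrow reading but not certain.
- All adverse events and serious adverse events are to be recorded with no restriction by arm, and the SIDAS comes from surveys that both arms complete. A comparison by arm remains possible.

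Calling this the primary safety outcome would also be loose. Safety belongs to primary aim 1 but is absent from the 4.10 primary measures, no progression criterion rests on it, and section 4.12 rules out formal hypothesis testing.

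It can be added that 4.1 leaves the word linked undefined, that 4.14 asks for a causality assessment without making it a condition for counting, that section 4.14 gives endpoint adjudication to a committee with independent members, and that safety tables are commonly left to an analysis plan not seen here.

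These points narrow the concern but do not remove it. Recording all events is not the same as saying that all will be reported, and 4.1 is the sentence that says how safety is operationalised. The self-reported component does not supply an unfiltered count of recorded adverse events. A committee's adjudication would still be an attribution. An analysis plan would inherit two conflicting definitions, and the conflict lies in the protocol's own text.

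**Conclusion.** The contradiction is real. Section 4.1 filters the adverse-event component of safety by its link to the intervention, while section 3 and the 4.14 definition do not. Followed as written, that component rests on an attribution judgement and has no valid control-arm counterpart for events that also occur in the background.

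The effect is confined to that component. The self-reported component stands, and the data needed for an all-cause comparison are already to be recorded.

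The range of 1.25 to 20 points is an illustration only. It rests on assumed equal true rates of 5% to 20%, on 25% to 100% of intervention-arm events being judged linked, and on no control events being judged linked. If some control events tied to surveys or screening were counted, the spurious difference would be smaller. The point should be corrected before results are reported, but it does not call the design into question.

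**What to change.** Reconcile section 4.1 with sections 3 and 4.14. In objective 1 of 4.1:

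- Define the adverse-event component as all adverse events and serious adverse events, as 4.14 defines them, in both arms and regardless of attribution.
- State that they will be reported by arm, with counts and 95% confidence intervals.
- Keep self-reported adverse consequences as the second component.
- Show relatedness, as assessed under 4.14, only as a secondary tabulation.

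The cost is a change of wording. No new data are needed, because 4.14 already has every adverse event and serious adverse event recorded.
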